# BariSurg trial: Sleeve gastrectomy versus Roux-en-Y gastric bypass in obese patients with BMI 35–60 kg/m^2^ – a multi-centre randomized patient and observer blind non-inferiority trial

**DOI:** 10.1186/s12893-015-0072-7

**Published:** 2015-07-18

**Keywords:** Sleeve gastrectomy, Roux-en-Ygastric bypass, Randomized controlled trial, Patient and observer blind trial, Long-term excess weight loss, Obesity related co-morbidity, Gastroesophageal reflux disease, Quality of life, Morbidity, Mortality

## Abstract

**Background:**

Roux-en-Ygastric bypass (RYGB) and sleeve gastrectomy (SG) rank among the most frequently applied bariatric procedures worldwide due to their positive risk/benefit correlation. A systematic review revealed a similar excess weight loss (EWL) 2 years postoperatively between SG and RYGB. However, there is a lack of randomized controlled multi-centre trials comparing SG and RYGB, not only concerning EWL, but also in terms of remission of obesity-related co-morbidities, gastroesophageal reflux disease (GERD) and quality of life (QoL) in the mid- and long-term.

**Methods:**

The BariSurg trial was designed as a multi-centre, randomized controlled patient and observer blind trial. The trial protocol was approved by the corresponding ethics committees of the centres. To demonstrate EWL non-inferiority of SG compared to RYGB, power calculation was performed according to a non-inferiority study design. Morbidity, mortality, remission of obesity-related co-morbidities, GERD course and QoL are major secondary endpoints. 248 patients between 18 and 70 years, with a body mass index (BMI) between 35–60 kg/m^2^ and indication for bariatric surgery according to the most recent German S3-guidelines will be randomized. The primary and secondary endpoints will be assessed prior to surgery and afterwards at discharge and at the time points 3–6, 12, 24, 36, 48 and 60 months postoperatively.

**Discussion:**

With its five year follow-up, the BariSurg-trial will provide further evidence based data concerning the impact of SG and RYGB on EWL, remission of obesity-related co-morbidities, the course of GERD and QoL.

**Trial registration:**

The trial protocol has been registered in the German Clinical Trials Register DRKS00004766.

## Background

### Rationale of the trial

The effect of bariatric surgery on obesity and related co-morbidities such as type 2 diabetes mellitus (T2DM) or hypertension is no longer doubted [1–3]. Reliable data showing improved overall patient survival and a reduced cancer incidence, especially in females, following bariatric surgery are available [4]. Additionally, bariatric surgery can now be performed safely and with acceptable morbidity and mortality [5, 6]. The procedures performed in the field of bariatric surgery are still evolving and include rather simple procedures such as gastric banding and more advanced techniques, such as biliopancreatic diversion or ileal transposition. Looking from a more general point of view, Roux-en-Y gastric bypass (RYGB) and sleeve gastrectomy (SG) are the most commonly performed procedures worldwide and in Germany, a finding that is likely due to their positive risk/benefit correlation [6]. However, RYGB is still considered superior to SG [7, 8]. This belief, however, is mostly based on historical considerations, as RYGB was one of the first bariatric procedures ever performed [9]. Because of recent evidence including systematic reviews and randomized controlled trials, SG has become more and more accepted as a stand-alone bariatric surgery procedure [9–17]. The systematic review data revealed, among other things, that excess weight loss (EWL) after SG was not significantly different from EWL following RYGB, 24 months after surgery [13]. This finding is consistent with that of Peterli et al., who also observed no significant differences in 12 month post-op EWL between SG and RYGB [9]. Another randomized controlled trial (RCT) from Finland, comparing SG and RYGB, revealed a significantly reduced operative time and complication rates in favour of the SG group [12]. As a result, the German statistic on obesity surgery for 2011 revealed for the first time, that more SG resections than RYBGs were performed [13, 18, 19]. Nevertheless, SG is still regarded with some scepticism due to the lack of valid long-term results and RCTs. Major criticism includes not only the effect of SG on EWL, but also on the course of obesity-related co-morbidities, on gastroesophageal reflux disease (GERD), and on quality of life (QoL) [20–23]. Furthermore, it seems that SG is correlated with rather specific complications such as fistulas and/or stenosis. The incidence of these complications is reported with the range 0 % to 17.5 % [19]. However, SG has a rather fast learning curve and can be performed within a short operative time. In addition, SG is considered less technically challenging than RYGB, due to the lack of anastomosis. Based on these unresolved controversies, further RCTs comparing SG and RYGB are urgently needed. The available RCT’s show that the clinical efficacy regarding EWL and T2DM remission between both procedures are comparable [14, 15, 24]. This goes along with similar morbidity rates even though it seems that the morbidity rate of RYGB in these RCTs is higher [12, 15].

**Table 1 Tab1:** Inclusion and exclusion criteria

Inclusion criteria	Exclusion criteria
BMI 40-60 kg/m^2^	Lack of informed consent
BMI 35–40 kg/m^2^ with at least one obesity-related co-morbidity	Expected lack of compliance
Age 18–70 years	Previous bariatric surgery
	Pregnancy

### Objective

The primary endpoint of the BariSurg RCT, to compare EWL rates 2 years after SG and RYGB, was chosen based upon systematic review findings [13]. BariSurg will be a multi-centre, randomized controlled, patient and observer blind trial. Major secondary endpoints will be morbidity, mortality, re-operation rate, remission of obesity-related co-morbidities, the occurrence and course of GERD, QoL, the course of the dumping syndrome, and the EWL rate 60 months after surgery.

## Methods/Design

### Trial design

The BariSurg trial is a multi-centre, randomized controlled, patient and observer blind trial.

### Sample size

A total of 248 patients will be randomized, with 124 patients assigned to each treatment arm. A dropout rate of approximately 20 % is considered realistic and has been accounted for the total number of randomized patients.

### Patient selection criteria

Patients between 18 and 70 years old with a BMI between 35 and 60 kg/m^2^ with indication for bariatric surgery according to the most recent German S3 guidelines will be eligible. Patients with a BMI of 35–40 kg/m^2^ need to have at least one obesity-related co-morbidities such as T2DM or hypertension (see Table 1).

### Recruitment and timelines

Patients will be recruited by the above mentioned seven participating centres. The recruitment period is estimated at 18 months. The time from enrollment of the first patient to study completion of the last, will be approximately 78 months, and the proposed duration of the entire trial is 90 months.

### Randomization

Patients fulfilling all inclusion without meeting any exclusion criteria and after receiving their informed consent, randomization will be performed intraoperatively via an internet-based randomization tool (http://www.randomizer.at). Randomization is performed by block randomization and will be stratified for each centre until the enrolment goal of 248 patients has been reached.

### Interventions

Patients will be asked to complete standard preoperative diagnostics including esophagogastroduodenoscopy (EGD), endocrine assessment and psychosomatics, and will also fill out four questionnaires (Short-Form-36 Health Survey (SF-36) [25], Gastrointestinal Quality of Life Index (GIQLI) [26], the Dumping questionnaire (Sigstad score) and Gastrointestinal Symptom Rating Score (GSRS) [27, 28]). Two weeks before surgery, patients will be asked to reduce their weight by following a low calorie liquid diet [29]. Preoperatively, a single-shot antibiotic prophylaxis will be given. For the surgical procedure, the patient will be placed in the supine position 45° (reverse Trendelenburg).

### Roux-en-Y-gastric bypass

After the gastroesophageal junction is identified, the stomach is transsected with a linear stapler 6 cm below the junction. A pouch with a 4–6 cm height and 14–16 mm width is created using a 42 French tube. A 70 cm biliopancreatic limb is defined and an end-to-side gastroenterostomy will be performed using either a 30 mm linear or 25 mm circular stapling technique. The common channel (side-to-side jejunojejunostomy) will be stapled after another 150 cm antecolic limb. To identify a leak of the proximal anastomosis methylene blue is applied through a nasogastric tube [30]. All patients will be discharged with the recommendation of oral intake of multivitamin tablets twice daily. During the follow up examination vitamin levels will be assessed regularly. In case of vitamin deficiency substitution of vitamins will be performed.

### Sleeve gastrectomy

The gastroepiploic vessels are divided 6 cm prepyloric along the great curvature, until the angle of His and the left crus of the diaphragm are visible. Along with a 42 French bougie, the stomach is then resected using linear stapler devices. At the angle of His the stapler line is sutured. The sleeve is checked for leakage using methylene blue. All patients will be discharged with the recommendation of oral intake of multivitamin tablets twice daily.

### Study visits

Study documentation and visits of patients will be performed by both surgeons and study nurses. Since the trial is designed as observer and patient blind RCT, information about the surgical procedure will not be reported during the follow-up examinations. There will be 9 study visits during the BariSurg RCT (see Fig. 1). During the first postoperative year, study visits will be performed at discharge, 3–6 months and 12 months postoperatively. Then visits will be performed annually. Every postoperative study visit includes data collection of weight, morbidity, mortality, course of obesity-related co-morbidities (including laboratory parameters and current medication), analysis of nutritional supplementation, occurrence of GERD and analysis of dumping syndrome using the Sigstad score. In addition to the above mentioned information, extended study visits will yearly assess general laboratory parameters, EGD results and the questionnaires (SF-36, GIQLI, GSRS, see Fig. 1).

**Fig. 1 Fig1:**
[figure not shown]
Flow chart of BariSurg trial, showing the timeline and the course for trial participants. Abbreviations: BMI: body mass index, T2DM: type 2 diabetes mellitus, EWL: excess weight loss, EGD: esophagogastroduodenoscopy, SF-36: Short-Form-36 Health Survey, GIQLI: gastrointestinal quality of life index, GSRS: gastrointestinal symptom rate score, EWL: excess weight loss, GERD: gastroesphageal reflux disease

### Risk-benefit ratio

SG is associated with a morbidity rate between 0–17.5 % and a mortality rate between 0–1.2 % [13]. The most frequently occurring postoperative complications are insufficiencies/fistulas at the staple line, leakage, stenosis of the sleeve and dilatation of the sleeve [5]. RYGB has a morbidity rate of 2-10 % and a mortality of 0.5-0.8 % [7, 12, 15]. Frequently observed complications include anastomotic insufficiency, especially with regard to the gastrojejunostomy, and dumping syndrome. Dumping syndrome is observed in 42 % after RYGB and up to 29 % after SG [31–33]. Therefore patients will be assessed for dumping syndrome. If the diagnosis dumping syndrome is confirmed patients will get the optimal treatment for dumping syndrome [28]. For both bariatric procedures, nutritional supplementation might be necessary for the remainder of the patient’s life.

### Outcome

The summary of the primary and the secondary endpoints depicts different points of view concerning the efficacy and safety of bariatric procedures. In doing so, medical issues as well as patient assessment can be analyzed.

### Primary endpoint

The primary endpoint is defined as EWL at 24 months after surgery (RYGB or SG). Power calculation was made according to the systematic review of Fischer et al. [13].

### Secondary endpoints

Long-term EWL at 60 months after surgery, morbidity, mortality, course of obesity-related co-morbidities (T2DM, hypertension, joint pain, sleep apnoea, dyslipidemia), vitamin status, incidence and/or course of GERD and QoL (as defined by the SF 36) and dumping syndrome (as defined by the Sigstad score) will form the secondary endpoints. The course of obesity-related co-morbidities is assessed by laboratory examinations and current medication use. T2DM remission will be measured by HbA1c, fasting glucose and medication use. Hypertension will be monitored by medication and blood pressure measurements. The course of joint pain and dyslipidemia are assessed by pain and respectively lipid metabolism medication. The course of sleep apnoea is analysed by patients’ application of CPAP-mask. Nutritional substitution will be assessed using a questionnaire which was developed in the bariatric centre of the University of Heidelberg. GERD incidence and course of GERD will be assessed with EGD and by using GSRS and GIQLI as standardized questionnaires. To evaluate QoL, the validated SF-36 questionnaire will be used. The Dumping score will be evaluated by using the validated Sigstad score. Secondary endpoints will be evaluated preoperatively, at discharge, 3-6, 12, 24, 36, 48 and 60 months postoperatively. Questionnaires will be filled out 12, 24 and 60 months after surgery. The EGD will be performed 12 and 60 months postoperatively.

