### Secondary analyses

Concerning secondary endpoints, exploratory data analysis will be performed and appropriate summary measures for the empirical distribution, as well as descriptive two-sided p-values, will be calculated. Homogeneity of the treatment groups will be described by comparing the baseline values. Each patient’s allocation to the different analysis populations [full analysis set (FAS) according to the intention-to-treat (ITT) principle, per protocol (PP) analysis set, safety analysis set] will be defined prior to analysis and documented in the analysis plan prior to database closure. During the data review, deviations from the protocol will be assessed as 'minor' or 'major'. Major deviations from the protocol will lead to the patient's exclusion from the PP analysis set. In addition to the evaluation of PP, an ITT analysis will be performed as a sensitivity analysis.

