### Trial organization and administration

#### Ethical considerations

SG and RYGB are frequently performed, standard techniques in bariatric surgery. The overall complication rate in SG and in RYGB described by Birkmeyer et al. is 5.9 % and 10.3 % respectively. A mortality of 0 % in SG and 0.3-0.9 % in RYGB was observed [12, 15, 37]. All participating centres perform both techniques frequently. In this manner morbidity and mortality rate can be expected like above mentioned. Furthermore, all participating centres received positive approvals of the according ethic committees (i.e. the University of Heidelberg from the Heidelberg ethics committee (S500/2012), Johanniter Hospital (Bonn) (2015179/2014), Städtisches Klinikum Karlsruhe, Schwarzwald-Baar-Klinikum (Villingen-Schwennigen), Agaplesion Bethesda Krankenhaus Stuttgart from the ethics committee of the State Board of Physicians of Baden-Württemberg which is responsible for the mentioned hospitals (B-F-2014-059)). The Caritas-Krankenhaus St. Josef (Regensburg) requested formal information of the ethics committee of the Bavarian State Board of Physicians to be legally considered a positive ethic vote.)

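### The course of joint pain rests on pain medication alone, which is not specific to joint pain, and the schedule includes the discharge visit

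*Protocol article*

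**What the plan says.** The protocol article lists joint pain among the obesity-related co-morbidities whose course is a secondary endpoint. Its Secondary endpoints section sets a general rule, "The course of obesity-related co-morbidities is assessed by laboratory examinations and current medication use", and then a specific one: "The course of joint pain and dyslipidemia are assessed by pain and respectively lipid metabolism medication".

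On timing, the same section states: "Secondary endpoints will be evaluated preoperatively, at discharge, 3-6, 12, 24, 36, 48 and 60 months postoperatively". The Study visits section separately lists what every postoperative visit collects, and this includes the "course of obesity-related co-morbidities (including laboratory parameters and current medication". Discharge is one of those visits: "study visits will be performed at discharge, 3–6 months and 12 months postoperatively".

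On status, the Secondary analyses section states: "Concerning secondary endpoints, exploratory data analysis will be performed". P-values for these endpoints are descriptive.

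**The concern.** The specific rule treats pain medication and lipid medication as the same kind of evidence. A lipid drug points to its condition, whereas an analgesic does not, and the operation under study is itself a reason to take one. Followed as written, the rule can go wrong in three ways:

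- At discharge, and possibly at 3–6 months, analgesics taken because of the operation cannot be told apart from analgesics taken for a joint.
- At later visits, a patient whose joint pain has gone but who takes analgesics for another reason looks like a patient with persisting joint pain, so remission is understated.
- A patient with joint pain who takes no medication looks free of it. If that is so before surgery, an improvement cannot be seen.

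At stake is the interpretability of one listed secondary endpoint. The Objective section names remission of co-morbidities among the major secondary endpoints, and the Discussion counts their course among the questions the trial should answer.

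**Working it through.** **Step 1. Compare the measures named for each co-morbidity (Secondary endpoints section).**

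| Co-morbidity | Measure named | Specific to the condition? |
|---|---|---|
| Type 2 diabetes | HbA1c, fasting glucose, medication | yes, with a direct measure |
| Hypertension | blood pressure, medication | yes, with a direct measure |
| Dyslipidemia | lipid medication | yes |
| Sleep apnoea | use of a CPAP mask | yes |
| Joint pain | pain medication | no |

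The general rule adds laboratory examinations, but no laboratory test is named for joint pain. The questionnaires do not fill the gap either: the article assigns them to quality of life, reflux, dumping and nutritional substitution. Joint pain is the only listed co-morbidity that rests wholly on a non-specific proxy.

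**Step 2. Compare the measure with the schedule.** The two schedule statements, in the Secondary endpoints and Study visits sections, agree that discharge is included. Neither makes an exception for joint pain.

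**Step 3. Size.** The plan states no figure on this point, so there is none to reproduce. It gives no rate of joint pain or of analgesic use. What follows shows only the form of the distortion, and every input is an assumption.

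*Apparent prevalence at a visit.* Let p be the share with joint pain who take analgesics, and q the share of all others who take analgesics for another reason. Then

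apparent share = p + (1 − p)q.

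| p | q = 5 % | q = 10 % | q = 60 % | q = 90 % |
|---|---|---|---|---|
| 10 % | 14.5 % | 19 % | 64 % | 91 % |
| 30 % | 33.5 % | 37 % | 72 % | 93 % |
| 50 % | 52.5 % | 55 % | 80 % | 95 % |

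For example, 0.30 + 0.70 × 0.10 = 0.37 and 0.30 + 0.70 × 0.90 = 0.93. When q is high, as it may be at discharge, the apparent share says almost nothing about p: across the three rows it runs only from 91 % to 95 %. When q is low, as it may be at 12–60 months, the distortion is modest.

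*Remission among patients with treated joint pain at baseline.* Let t be true remission and u the share of remitted patients who take analgesics for another reason. Then observed remission = t(1 − u). With assumed t of 50 % and 65 % in the two arms and the same u in both:

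| u | Observed | Difference |
|---|---|---|
| 0 % | 50.0 % and 65.0 % | 15.0 points |
| 10 % | 45.0 % and 58.5 % | 13.5 points |
| 20 % | 40.0 % and 52.0 % | 12.0 points |
| 30 % | 35.0 % and 45.5 % | 10.5 points |

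The absolute gap shrinks by the factor 1 − u. The ratio stays at 50/65 = 0.77. This shows dilution, not bias in favour of one arm.

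**The case against.** The strongest reply is that the article never says that every analgesic counts. It gives no rule for turning medication into a course, and an indication field or coding rule may sit in the case report form, the full protocol or the analysis plan, none of which is shown. The Data management section also provides for plausibility checks and queries to the investigator. This stands: scoring of analgesics for any indication is an inference from silence. What remains is that the one measure the article states is non-specific. An indication field would also not find patients with untreated joint pain.

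Second, the sentence on evaluation times covers all secondary endpoints together and cannot hold literally for each, since the list includes weight loss at 60 months. This too is fair. But the Study visits section separately collects the course of co-morbidities and medication at every postoperative visit. Collecting discharge data does not prove that they will be analysed as joint-pain course; the article simply does not rule it out.

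Third, for joint pain the endpoint is the course of a co-morbidity, whereas incidence is mentioned only for reflux. So the text does not support saying that a patient without baseline joint pain becomes a new case at discharge.

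A reader might also infer a bias against bypass, because the Ethical considerations section reports an overall complication rate for sleeve and bypass that "is 5.9 % and 10.3 % respectively", a gap of 10.3 − 5.9 = 4.4 points. The article does not support that inference. Its Risk-benefit ratio section gives overlapping morbidity ranges (0–17.5 % for sleeve, 2–10 % for bypass), its Unblinding section treats complication rates as similar, and nothing says what share of complications leads to lasting analgesic use.

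**Conclusion.** The point holds as a cheap improvement to a stated outcome rule, not as a proven error. The article measures joint pain by a proxy that cannot separate it from other pain, and schedules that measure at a visit where postoperative analgesia is to be expected. Discharge values, and possibly those at 3–6 months, may be confounded. Later values may be diluted to an unknown degree, and untreated joint pain is missed.

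A reader might go further and conclude that the whole derived course is wrong. The article does not support this: the 12–60 month course against baseline need not be wrong if few patients then take analgesics for other reasons. The size cannot be computed from the article, and the figures above rest wholly on assumed inputs. The endpoint is exploratory, and the primary non-inferiority conclusion is untouched.

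**What to change.** Four changes would settle the point:

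1. Record the indication with the medication entry that each visit already collects.
2. Add one yes/no question on joint pain at each follow-up visit.
3. Define the course among patients with joint pain at baseline, from the presence of joint pain together with use of an analgesic taken for it.
4. Leave the discharge visit out of the joint-pain course.

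If the case report form already records the indication, the first change reduces to saying so in the Secondary endpoints section. The cost is one extra field and one extra question on the form, plus a short change of text. The downside is that visits already completed lack these items. Recruitment began in November 2013, so the new definition could be applied in full only to later visits, and baseline joint-pain status for patients already enrolled would have to come from what was recorded at the time.
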